## Assignment of interventions: blinding

### Who will be blinded {17a}

This trial is a double-blind design, with subjects and investigators (including outcome measures and statisticians, etc.) not aware of the grouping. The physician who injected the drug is unblinded in this trial as the test drug used in this trial is a colorless, clear liquid with a different appearance to the cloudy glucocorticoid liquid used in the control group. This physician is not involved in the rest of the trial and must be out of the view of the subject and investigator when preparing the drug and injecting it.

### Procedure for unblinding if needed {17b}

There is an emergency unblinding contingency letter, which is numbered to match the subject number and contains instructions for the study drug grouping. If a serious adverse event occurs requiring emergency unblinding, the investigator will open the blinded envelope with the appropriate subject number to determine the drug grouping of the subject.

## Data collection and management

### Plans for assessment and collection of outcomes {18a}

Data collection will be conducted by questionnaire and automatically stored in a mobile database. The database will be collaboratively managed by the research team. Subsequent data analysis will be performed by the statistical analyst, ensuring that both the allocation and the intervention protocol remain blinded.

### Plans to promote participant retention and complete follow-up {18b}

To improve patient retention, we planned a short-term follow-up (4 weeks) to maximize the completeness of data collection and minimize the risk of dropout.

### Data management {19}

#### Data collection

Two testers will assess each subject on each of the scales in strict accordance with the requirements of the test. The “Basic Profile Questionnaire” and the results of each scale for each subject should include the number, date of assessment, and name of each subject.

#### Data recording

The original medical record and the CRF results should be recorded truthfully and carefully as required and the contents should not be changed once completed. If a correction is required due to a genuine error, the original record should not be altered, but only by means of an additional narrative, signed and dated by the responsible study physician.

All results from clinical trials are verified in detail and documented as early as possible to ensure that the data is authentic and reliable.

The various equipment, instruments, and drugs used in clinical research should have strict quality and safety standards and be guaranteed to be used under normal conditions.

### Confidentiality {27}

To ensure privacy, each patient will be assigned an ID number to hold personal information and contact details.

### Plans for collection, laboratory evaluation, and storage of biological specimens for genetic or molecular analysis in this trial/future use {33}

No biological specimens will be collected in the present study.

## Statistical methods

### Statistical methods for primary and secondary outcomes {20a}

All statistical inferences will be performed by two-sided test, the test level of statistical significance is set as 0.05, and the confidence interval of parameters is 95%. The count data describe the number of cases and percentage, and the measurement data describe the mean, standard deviation, minimum, maximum, median, and 25th and 75th quantiles. The counting data give the frequency distribution and the corresponding percentage. Qualitative data give the number of cases of positive rate, positive number, and denominator.

Shapiro–Wilk test will be used to verify the normality of the variables. For normally distributed variables, continuous variables are represented by “mean ± standard deviation”; for data that is not normally distributed, it is represented by “median, interquartile.”

In the analysis of baseline data, the independent sample *t* test will be used to compare the normal distribution between the measurement data groups. The non-normal distribution data are presented with median and interquartile intervals. Mann–Whitney *U* test will be used to compare ordered categorical variables between groups.

Repeated measures ANOVA will be used to study the independent effects, main effects, and interactions of time and grouping. *p* < 0.05 is considered statistically significant. Intentionality and protocol sets will be used to analyze primary and secondary outcomes. The results of intentionality treatment analysis are compared with those of protocol set analysis to determine whether the results are consistent. Missing data are processed as multiple imputation. Adverse events will be listed and analyzed using chi-square tests or Fisher precision tests. We analyzed test results using the IBM SPSS24.0 software.

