### Objectives {7}

The primary aim is as follows: to investigate whether shoulder joint cavity injection of botulinum toxin compared with corticosteroids (tretinoin acetate) significantly improves shoulder pain in patients with HSP without biceps tendinitis or acromionic bursitis.

The secondary aims are as follows: in patients with HSP without tendon synovitis or acromioclavicular bursitis, does shoulder joint cavity injection of botulinum toxin type A significantly affect cerebral hemodynamics, improve Fugl-Meyer upper limb motor function, improve passive shoulder motion, and improve Ashworth scale scores compared to glucocorticoids (tretinoin acetate)?

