### Outcomes {12}

All assessments (VAS, upper limb Fugl-Meyer scores, passive range of motion (ROM) improvement, spasticity (MAS) improvement) and information regarding painkiller use will be applied at the baseline and 1-week and 4-week follow-up visits. The VAS pain assessment is the level of pain experienced by the patient during the past week of passive shoulder motion. fNIRS assessments include dorsolateral prefrontal area (DLPFC), primary motor area (M1), primary sensory area (S1), and oxyhemoglobin versus total hemoglobin levels, which will be checked at baseline and 1-week and 4-week follow-up. Other measures including demographics, history taking, and ultrasound of the shoulder joint in the study will be recorded at screening only. Adverse events are documented as described in the results.

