#### fNIRS assessments

This experiment used a portable near-infrared functional brain imager (NirSmart, Danyang Huichuang Medical Equipment Co., Ltd., China) to record the cortical activation state. Our equipment consisted of 13 light sources and 15 detectors, making up a total of 35 channels, with an average distance between light sources and detectors of 2.7 cm. Reference was made to the international 10–20 system for localization [33], with the Cz point and Fpz point marked as standard localization points.

Subjects carry a special backpack to carry the fNIRS mainframe which transmits the data to the computer via wireless mode. Based on previous studies, the present study selected bilateral DLPFC, M1, and S1, which have been shown to be associated with sensory function, for testing. In this study, we examined bilateral PFC and S1 brain regions associated with sensory functions, and their channels corresponded to cortical distributions in CH17, CH20, CH22, CH26, CH27, CH31, CH36, CH43, CH48, and CH49. During the fNIRS test, the room temperature is kept at a comfortable constant, and the room is kept quiet. The patient is guided by audio to remain quietly in a seated position (Fig. 4) and is informed that self-activity and communication are prohibited during the test. Measurements will be taken in the resting state and in the shoulder joint external rotation and abduction state, three times in each state and averaged.

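### The secondary aim on cerebral hemodynamics names no deciding fNIRS contrast, the article disagrees with itself on regions and signals, and every test is read at 0.05, so a false positive for that aim is likelier than 5%

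*Protocol article*

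**What the plan says.** Objectives {7} includes, among the secondary aims, one yes/no question on brain activity: "does shoulder joint cavity injection of botulinum toxin type A significantly affect cerebral hemodynamics" relative to glucocorticoid.

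The variables that could answer it are described in two places.

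- Outcomes {12}: "fNIRS assessments include dorsolateral prefrontal area (DLPFC), primary motor area (M1), primary sensory area (S1), and oxyhemoglobin versus total hemoglobin levels", at baseline, 1 week and 4 weeks.
- The fNIRS assessments subsection, on regions: "the present study selected bilateral DLPFC, M1, and S1". The next sentence says: "we examined bilateral PFC and S1 brain regions associated with sensory functions", and lists channels for those areas only.
- The same subsection, on states: "Measurements will be taken in the resting state and in the shoulder joint external rotation and abduction state". It goes on to say that the data analysis concentrates on HbO, that values are averaged within a region, and that task is compared with rest.

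The testing rule is in Statistical methods {20a}: "All statistical inferences will be performed by two-sided test, the test level of statistical significance is set as 0.05". For the outcomes over time: "Repeated measures ANOVA will be used to study the independent effects, main effects, and interactions of time and grouping". The article then says that p < 0.05 "is considered statistically significant. Intentionality and protocol sets will be used to analyze primary and secondary outcomes". It does not say which fNIRS result decides the aim, and it mentions no adjustment for several tests.

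**The concern.** The aim is phrased as one question about significance, but many results could be offered as its answer: several regions, on two sides, under more than one movement, possibly for two hemoglobin signals, each with a group effect and a group-by-time effect. With each read at 0.05 and none designated, the text allows a yes from whichever one is significant. The error rate for the aim is then not 5%, and it cannot be stated at all until the set of variables is fixed.

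The conflict between the descriptions makes this worse, because it leaves open which variables belong to the analysis. At stake is the mechanistic conclusion. The article presents fNIRS as one of its two innovations and as the objective complement to self-reported pain, so a chance result in one region could be read as the mechanism of the drug.

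**Working it through.** **Inputs from the article.** Two-sided 0.05 for all inferences and both main effects and interactions ({20a}); three visits (Outcomes {12}); 32 per group before allowance for losses (Sample size {14}). The 32 reproduces: d = 1/1.4 = 0.714, and a two-sample t test with 32 per group has 80.3% power. It is used below only as the group size. The article gives no count of fNIRS tests and no error rate for the fNIRS aim, so there is no stated figure to reproduce on that point.

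**Which effects count.** Two omnibus tests per outcome compare the drugs: group, and group-by-time. The time main effect does not compare them and is left out.

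**Size of the set, by reading.**

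- Narrow: bilateral PFC and S1, HbO, one task-versus-rest contrast: 2 × 2 = 4 outcomes.
- Middle: bilateral DLPFC, M1 and S1, HbO, two movements: 6 × 2 = 12 outcomes.
- Wider: the same six regions, HbO, three states: 6 × 3 = 18 outcomes.
- Widest: six regions, three states, two signals: 6 × 3 × 2 = 36 outcomes.

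**Independent tests.** The chance of at least one p < 0.05 among k tests is 1 − 0.95^k.

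- k = 4 (narrow, interaction only): 18.5%
- k = 8 (narrow, both effects): 33.7%
- k = 24 (middle, both effects): 70.8%
- k = 36 (wider, both effects): 84.2%
- k = 72 (widest, both effects): 97.5%

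**Correlated outcomes.** HbO from different regions and states in one person is likely to be correlated, and the article gives no value, so 0 to 0.9 is an assumed range. Simulation: two arms of 32, three visits, correlation between visits 0.5 (assumed), equal correlation between outcomes, sphericity, no true difference, F tests for group and group-by-time at 0.05, 2,000 runs per cell. Chance of at least one false positive:

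| Outcomes | Effects read | r = 0 | 0.3 | 0.5 | 0.7 | 0.9 |
|---|---|---|---|---|---|---|
| 4 | group-by-time | 19% | 17% | 16% | 14% | 11% |
| 4 | both | 34% | 30% | 29% | 26% | 20% |
| 12 | group-by-time | 46% | 40% | 33% | 23% | 14% |
| 12 | both | 71% | 64% | 52% | 42% | 26% |
| 18 | both | 85% | 75% | 64% | 47% | 30% |
| 36 | both | 97% | 93% | 80% | 62% | 32% |

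The Monte Carlo standard error is at most √(0.25/2000) = 1.1 percentage points. Separate runs gave 19% or 20%, and 25% or 26%, for the lower ends of the two-effect rows with 4 and 12 outcomes; the lower figures are used in the conclusion.

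**Naming a variable is not enough.** A single outcome with both effects read at 0.05 has a chance of 1 − 0.95² = 9.75% if the two tests are independent. The effect has to be named as well.

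**The case against.** The case on the other side has five parts.

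- *The outcome is secondary and mechanistic, and a separate plan may exist.* Unadjusted secondary testing is common, and Interim analyses {21b} refers to a statistical plan that is not shown. This stands in part. The absence of an adjustment can be stated only of this article, and nothing here touches the VAS conclusion. But the article does set a rule for all inferences, words this aim as a significance question, and contradicts itself on the variables. Those are faults in the text at hand. The point also does not ask for correction across VAS, Fugl-Meyer, range of motion and Ashworth scores.
- *The narrow reading is the natural one.* HbO, regional averages and task versus rest, together with the emphasis on PFC and S1 in the Discussion, point to a small set. That is fair, and the narrow reading is computed first. It still gives 11–19%, and the article does not settle on it: Outcomes {12} and the footnote to Table 1 keep M1.
- *The group main effect is a poor test of the drugs,* because one of the three visits precedes the injection. This is right, so the interaction-only figures are shown separately. But {20a} says that main effects are studied too.
- *No sentence says that any p < 0.05 answers the aim yes.* This is correct. A reader might infer such a rule, but the text only allows it. That a chance region would be reported as the mechanism is likewise a risk, not something planned.
- *A false yes is not shown to be more likely than not.* A reader might infer that it is from the widest grid. Fourteen independent tests are needed to pass 50% (13 give 48.7%, 14 give 51.2%). With both effects read, the simulation passes 50% for 12 and 18 outcomes up to a correlation of about 0.5, and for 36 outcomes up to 0.7. It does not pass 50% for four outcomes or for strongly correlated signals. The documents do not support the stronger claim.

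**Conclusion.** The point holds as a range. The hemodynamics aim has no designated fNIRS contrast, the article conflicts on regions and signals, and each test is read at 0.05 with no adjustment stated here. If any significant result is taken as a yes, the chance of at least one false positive when the drugs do not differ is:

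- about 11–19% with four regional HbO outcomes and group-by-time only;
- 19–34% with the same four outcomes if the group effect is also read;
- about 25–71% with six regions, two movements and both effects, and higher for wider grids.

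The lower ends assume a correlation of 0.9 between outcomes and the upper ends assume none. That the rate exceeds 5% is robust across these readings; its exact size is not known, because it depends on a grid and a correlation that the article does not fix. The matter is confined to a secondary aim and leaves the primary VAS conclusion as it is.

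**What to change.** First, reconcile the regions and signals between Outcomes {12} and the fNIRS assessments subsection: state whether M1 is analysed, whether the frontal region is DLPFC or PFC, and whether total hemoglobin is an outcome.

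Second, in {20a}, name one contrast that decides the hemodynamics aim and test it at 0.05. An example is the between-group difference in change from baseline of the HbO task-minus-rest response, averaged over the two movements, in one pre-named region at one named visit. This brings the false-positive rate for the aim back to 5%. If both PFC and S1 are to be kept, define one such contrast for each and apply Holm: the smaller p-value against 0.05/2 = 0.025 and, if that passes, the other against 0.05.

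Third, state that all other regions, total hemoglobin, single movements and single channels are exploratory, reported with estimates and 95% confidence intervals and without a claim of significance.

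The cost is a few sentences before unblinding, with no new data or patients. A real effect confined to a region that was not named can be reported only as exploratory, and Holm over two regions loses a little power.

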### Sample size {14}

This study is a randomized controlled trial with botulinum toxin injections in the experimental group and glucocorticoid (tretinoin acetate) injections in the control group. The main regression indicator observed is the VAS pain score.

In this study, the sample size will be calculated with reference to similar relevant literature and pre-experimental results. The sample size will be calculated using two independent sample mean validity tests using the G-Power version 3.1.2 software. It is assumed that the means of the two groups are equal at baseline, that there is a 1-point difference in VAS pain score between the two groups at the first post-treatment assessment, and that the standard deviation of the two groups was 1.4, which should be consistent at each subsequent assessment, measured as an effect size (i.e., Cohen *d*, 0.71). Based on these magnitudes, alpha = 0.05 two-tailed is set. To achieve 80% efficacy, 32 patients per group will be counted as study subjects. To compensate for potential loss to follow-up, approximately 20% of patients will be added, with a final inclusion target of 78 patients (39 in each group).

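### The trial is sized for a two-group comparison of VAS at one visit but analysed by repeated-measures ANOVA, and no effect or visit is named as deciding it

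*Protocol article*

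**What the plan says.** All places are in the protocol article.

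- **Sample size {14}.** The method is a two-sample comparison of means: "The sample size will be calculated using two independent sample mean validity tests using the G-Power version 3.1.2 software". The inputs are no baseline difference ("It is assumed that the means of the two groups are equal at baseline") and a post-treatment difference stated as "there is a 1-point difference in VAS pain score between the two groups at the first post-treatment assessment", with SD 1.4 (Cohen d 0.71). The error rate is given by "alpha = 0.05 two-tailed is set" and the result by "To achieve 80% efficacy, 32 patients per group will be counted as study subjects". About 20% is added, giving 39 per group and 78 in all.
- **Outcomes {12}.** VAS and the other scales "will be applied at the baseline and 1-week and 4-week follow-up visits". By this schedule the first post-treatment assessment is week 1.
- **Abstract, Methods.** The primary outcome is change in VAS, without a time point.
- **Statistical methods {20a}.** The t test is named for baseline data only. The between-group analysis named for the outcomes is: "Repeated measures ANOVA will be used to study the independent effects, main effects, and interactions of time and grouping". Significance is read at 0.05, in intention-to-treat and per-protocol sets, with multiple imputation. No effect is singled out as primary, and baseline VAS is not named as a covariate.

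**The concern.** A power statement belongs to one test. Here it belongs to a comparison of two means at one visit, while the analysis section offers a family of effects from a three-visit ANOVA. These effects answer different questions. The group main effect averages the group difference over the time levels and, if baseline is one of them, averages in a difference that randomisation makes zero on expectation. The interaction has 2 degrees of freedom and shows only that the two profiles are not parallel.

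Two things are at stake. First, the achieved power may differ considerably from 80%, in a direction that depends on the effect chosen and on a correlation the article does not give. Second, with no deciding effect fixed, the choice could be made after the results are known. The article also plans an interim analysis at 39 patients, so the ambiguity could matter before the trial ends.

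**Working it through.** **Inputs from the article:** difference 1, SD 1.4, baseline difference 0, two-sided alpha 0.05, n = 32 per group (39 after inflation), visits at baseline, week 1 and week 4.

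**Assumptions not in the article:**
- Baseline is a level of the time factor.
- The 1-point difference holds at week 4 as well as week 1.
- The correlation r between any two visits is the same, with equal SDs. Values of r are shown as a range.

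**Step 1: the plan's own figure.** d = 1/1.4 = 0.714. The noncentral t test with 62 degrees of freedom gives power 0.803 at n = 32 (0.798 with d rounded to 0.71). Inflation: 32 × 1.2 = 38.4, rounded up to 39; 2 × 39 = 78. Both stated figures reproduce.

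**Step 2: group main effect over three time levels.** The mean difference is (0 + 1 + 1)/3 = 0.667. The SD of a patient's three-visit mean is 1.4 × √((1 + 2r)/3). So d = 0.667 / [1.4 × √((1 + 2r)/3)], tested as a two-sample t test.

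**Step 3: group-by-time interaction.** The squared deviations of (0, 1, 1) from their mean sum to 2/3. Noncentrality is (n/2) × (2/3) / [1.96 × (1 − r)], which at n = 32 is 16 × 0.667 / [1.96 × (1 − r)]. The degrees of freedom are 2 and 124.

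**Step 4: baseline-adjusted difference at one visit.** The residual SD is 1.4 × √(1 − r²), so d = 1 / [1.4 × √(1 − r²)].

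| r | Main effect d | Main effect power, n = 32 | Main effect power, n = 39 | Interaction noncentrality | Interaction power, n = 32 | Adjusted one-visit power, n = 32 |
|---|---|---|---|---|---|---|
| 0 | 0.825 | 90% | 95% | 5.44 | 53% | 80% |
| 0.1 | 0.753 | 84% | 91% | 6.05 | 58% | 81% |
| 0.3 | 0.652 | 73% | 81% | 7.77 | 69% | 84% |
| 0.5 | 0.583 | 63% | 72% | 10.88 | 84% | 90% |
| 0.7 | 0.532 | 55% | 64% | 18.14 | 97% | 98% |

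The main effect crosses 80% at r of about 0.17 with 32 per group, and about 0.32 with 39. The interaction reaches 80% from r of about 0.45 with 32 per group. A simulation at r = 0.5 and n = 32 gave 0.636 for the main effect and 0.845 for the interaction, in agreement.

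**Step 5: sensitivity to the assumptions.** If only the two post-baseline visits enter the ANOVA, there is no dilution, and the group effect has 98%, 90% and 86% power at r = 0, 0.5 and 0.7. If the difference is absent at week 4, main-effect power is 37% at r = 0 and 18% at r = 0.7.

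**Step 6: error rate if either effect counted as success.** For two independent tests at 0.05 it would be 1 − 0.95² = 0.0975. Simulations under no effect at r = 0.3 to 0.7 gave about 9% to 10%.

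**The case against.** The strongest reply is that the article does not show the analysis to be underpowered. Four parts of it deserve an answer.

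- **The shortfall is conditional.** It needs baseline in the time factor, which is the natural reading of three visits and no named covariate but is not stated. It also needs a correlation above about 0.17. Change in VAS could be analysed after baseline only, and then the main effect exceeds 80% at the correlations computed. The interaction does too from r of about 0.45. This stands: a reader might infer that the ANOVA fails to deliver 80% power, but the documents do not support that as an unconditional statement.
- **The sized test may still be run.** The ANOVA sentence lists independent effects separately from main effects and interactions. This may mean the group comparison at each visit, and the same section promises 95% confidence intervals. It would therefore go too far to say that the powered test will not be performed, or that no treatment difference with an interval will be reported. Even on this reading, neither the visit nor the deciding effect is named.
- **No either-test rule is written.** The 9–10% error rate describes a rule that the article neither states nor excludes. It illustrates the risk and is not a property of the plan.
- **Covariates and pooling belong in an analysis plan.** Repeated-measures ANOVA is conventional for three visits, and leaving out a baseline covariate is a loss of efficiency, not an error. This stands too.

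What the reply does not remove is that the article itself states both the sizing test and the analysis, and nothing in it connects them.

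**Conclusion.** The point holds in a limited form. The stated 32 per group is correct for the comparison it was calculated for. The analysis section names a different method and leaves open which effect and visit decide the trial, so the 80% is not attached to a defined primary test.

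With baseline as a time level and a difference that persists to week 4, main-effect power ranges from 90% (r = 0) to 55% (r = 0.7) at 32 per group, while interaction power runs the other way, from 53% to 97%. At r = 0.3 neither reaches 80%. Because the two move in opposite directions, the choice between them has real consequences. These figures are illustrations that rest on assumed correlations and on the stated readings of the design. Severity: should fix.

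**What to change.** In Statistical methods {20a}, name one primary test: the between-group difference in VAS, with its 95% confidence interval, at the visit used for sizing (the first post-treatment assessment, week 1). If the sponsor prefers week 4, use that visit and restate Sample size {14} to match.

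Estimate the difference in the intention-to-treat set from an ANCOVA, or a mixed model on post-baseline VAS, with baseline VAS as covariate. Pool that single contrast over the imputations. An estimate with a standard error pools directly, which omnibus F tests do not. Present the ANOVA main effects and interaction as supportive.

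The cost is wording and slightly more model specification. No extra data or patients are needed: under the article's difference and SD, the contrast has at least 80% power with 32 per group at any correlation. The change should be made before any outcome data, including the interim data, are seen.
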